### Recruitment

Recruitment will be time-dependent in that a minimum number of trial participants with expected delivery dates (EDDs) that are within 8 weeks of each other must be recruited within 6 weeks in each site for each delivery of gFNP, namely at least 16 and ideally 20 (8 to 10 intervention and 8 to 10 control) with a maximum number per group of 12. In the recruitment process, community midwives will identify women using the initial criteria of age, parity and gestation. Guidelines will also be provided about the specific EDDs that are required for each gFNP delivery in each site.

Midwives will give all potentially eligible women a brochure describing the study, asking for agreement to give their names and contact details to the local researcher as part of a staged consent process, using an ‘agreement to contact’ form. Those agreeing will be contacted by the local researcher. The first contact will be by telephone to establish eligibility. Women who are not eligible will be thanked for their time. Those who are eligible will be given further information about the trial, and time to think about participation. After at least 24 hours, the researcher will contact the women by telephone and if telephone agreement is given the researcher will make a home visit, obtain written consent and collect baseline data. Participants will be reminded about the services available in their area and that they should keep their next midwifery appointment and remind them about the next research contact. After leaving, the local researcher will telephone the central randomization service provided by HSRU Aberdeen to randomize the participant, giving identifying details and sufficient prognostic detail to allow minimization. Researchers will be given a study number for the participant but will remain blind to allocation, which will be conveyed by HSRU Aberdeen to LSHTM CTU by secure Email.

LSHTM CTU will inform all participants by first class post of their allocation to the intervention or control arm of the study. For women in the intervention arm, the LSHTM team will inform the relevant FNP team by fax, receipt confirmed by fax, of the women in the intervention arm so that the gFNP intervention can be initiated. This process will continue until at least 16 and no more than 24 women have been recruited in each site for the first delivery of gFNP. If a second group is to be offered in the same location, a second round of recruitment will take place 12 weeks later, repeating the same process.

As a strategy to limit attrition, participants will be given ‘High Street’ vouchers for £20 at each home-visit data collection point (baseline, two months postpartum and twelve months postpartum) and a £10 voucher will be posted after the six month telephone contact as acknowledgement of their contribution, and to encourage continuation with the study. In addition, details of changes of address will be solicited by providing pre-paid addressed envelopes and response cards at baseline by sending birth congratulation cards and one year birthday cards.

### Data collection instruments

#### Primary outcome measures

Two primary outcome measures of parenting are being used because of the difficulties associated with the detection of low frequency events such as child abuse. One is a self-report measure of parenting opinions and the others an objective measure of parent-infant interaction. Both are known to be able to identify mothers at risk for abusive parenting.

The revised AAPI-2 [39] is a 40 item self-report measure able to discriminate between abusive and non-abusive parents. It includes five subscales: ‘inappropriate’ expectations of children, inability to demonstrate empathy to children’s needs, strong belief in the use of corporal punishment, reversing parent–child family roles and oppressing children’s power and independence. Responses are on a five-point Likert-type scale ranging from‘strongly agree’ to ‘strongly disagree’. Internal reliability of the subscales ranges from .83 to .93, Cronbach alphas range from .80 to .92. The scales were constructed based on factor analysis to demonstrate construct validity and the inventory has discriminant validity comparing abusive and non-abusive parents (sample 1,985).

The observational CARE Index [40,41] is based on a video recording of three minutes mother-child play, and measures three aspects of maternal behavior (sensitivity; covert and overt hostility; unresponsiveness) and four aspects of infant behavior (cooperativeness; compulsive compliance; difficultness; and passivity). These are highly correlated with attachment and differentiate between abusing, neglecting, abusing and neglecting, marginally maltreating, and adequate dyads [42]. Scores range from 0 to 14, higher scores indicating better sensitivity and/or co-operation. Scoring will be conducted blind to allocation.

In addition the incidence of child abuse during the child’s first year will be assessed by the number of case conferences; the number of children with Child Protection Plan in place; and the number of children removed from the home (all based on maternal reports at 12 months). The child’s attendance at hospital A&E departments for non-accidental injuries or ingestions of toxic substances will be confirmed using hospital episode statistics (HES) data.

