The sites delivering gFNP are established FNP sites and gFNP will be delivered in addition to the one to one FNP program in those sites, to clients who would are ineligible for FNP. The program is delivered to each group by two family nurses trained according to US NFP guidelines and who are experienced in delivering home-based FNP [26], one of whom is a practising midwife. Each group comprises between 8 and 12 women, whose partners are encouraged to attend. Women using group based antenatal care such as the Centering Pregnancy Model [27], reported a preference for this approach over traditional care [28-30]. Centering Pregnancy has been associated with improved prenatal outcomes such as reductions in preterm births among high-risk women [31,32]. Following this model of delivery, gFNP provides routine midwifery care in pregnancy and infant health checks according to NICE guidelines [33] during the gFNP session with encouragement for mothers to conduct the necessary pregnancy checks themselves with guidance from the family nurses and midwives. Any out-of-hours antenatal care is managed according to local arrangements (this may involve a community midwifery team or hospital) and intrapartum care is managed by the hospital/birth center midwifery team. The group context should help mothers to develop social networks with other local mothers [34], and to benefit from peer-group learning. Also, meeting in Children’s Centers helps families to become familiar with the other services and to develop regular contact with other professionals when additional support is called for [35].

An implementation evaluation in England found that both the mode of delivery and materials were acceptable to clients and nurses [34-36]. In addition to developing relationships with the family nurses, clients have developed close relationships with group members and made regular use of other services in the Children’s Centers. The delivered content of gFNP is consistent with NFP US National Office recommendations [36] and the prediction is that gFNP is likely to be associated with the same kinds of benefits as the individually delivered program. However, in order to provide optimal information for service providers and commissioners, and to provide the most effective support for potentially vulnerable families, it is important that programs be subject to rigorous randomized trials to provide evidence about efficacy and cost-effectiveness.

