### Study setting

Sites were included if they responded to an invitation to take part from the FNP National Unit, could demonstrate sufficient women of the relevant age and parity who had given birth in the previous year, and could confirm good links with community midwifery, who also had to sign the expression of interest. Only FNP teams who had delivered the home-based FNP program in its entirety (from birth to child age 24 months) to a cohort of women and with a practising midwife in the team were eligible.

The gFNP program is delivered by two family nurses, one of whom is a practising midwife, in community settings such as Sure Start Children’s Centers, located so that the amount of travelling necessary by group participants is kept to a minimum. Proximity to the location should enhance the rate of attendance and also foster the formulation of social networks. However, so that women from a potentially wider range of home addresses can be recruited to ensure the sample size, funds are available to reimburse intervention participants for travel by public transport to the intervention sessions. Child care is available for any other children. The gFNP program runs from approximately the 16th week of pregnancy to when the babies are 12 months old, meeting weekly or fortnightly during the daytime depending on the stage of the program (14 pregnancy sessions and 30 infancy sessions).

The control group mothers and infants would not be eligible for home-based FNP but will receive all the Universal Core Offer recommended in the Healthy Child Program through midwifery and health visiting services [37]. This is a substantial and universal service for expectant mothers and their infants with a strong evidence base [38] supported by systematic review evidence and NICE guidance. It offers screening tests, immunizations, developmental reviews, information and guidance to support parenting. The latest version has a strong emphasis on pregnancy and the first year of life. Community midwives and health visitors may provide or refer to a range of other community-based or specialist services designed to support young mothers.

Data collection for the study will be conducted by researchers blind to allocation in three visits to participant’s homes (baseline in pregnancy, when infants are two months and twelve months of age), and one telephone contact (when infants are six months old).

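### Child-protection case conferences, plans and removals are labelled incidence of abuse, but they depend on detection and on the 12-month visit, so an arm difference cannot be read as a difference in abuse

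*Protocol article*

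**What the plan says.** The protocol article, Primary outcome measures, names two primary outcomes, AAPI-2 and the CARE Index. It explains that it uses parenting measures because abuse is a low-frequency event and hard to detect. It then continues: "In addition the incidence of child abuse during the child’s first year will be assessed by the number of case conferences", followed by the number of children with a Child Protection Plan and the number removed from home. The source of these three counts is given as "all based on maternal reports at 12 months". One further item is checked against records: "The child’s attendance at hospital A&E departments for non-accidental injuries or ingestions of toxic substances will be confirmed using hospital episode statistics (HES) data".

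Professional contact in the two arms is described elsewhere:

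- **gFNP arm, Group Family Nurse Partnership section:** "The program is delivered to each group by two family nurses trained according to US NFP guidelines", and "gFNP provides routine midwifery care in pregnancy and infant health checks according to NICE guidelines" during the session.
- **gFNP arm, Study setting:** the groups run from pregnancy through the first year, "meeting weekly or fortnightly during the daytime depending on the stage of the program (14 pregnancy sessions and 30 infancy sessions").
- **Control arm, Study setting:** these families "will receive all the Universal Core Offer recommended in the Healthy Child Program through midwifery and health visiting services". No contact frequency is given.

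Data management states that HES records will be obtained for trial participants, covering all hospital activity from randomization to 12 months postpartum, including A&E.

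**The concern.** A case conference, a protection plan or a removal records that abuse or risk was suspected, that someone escalated it, and that services responded. It does not record abuse itself. The label equates the two and so fixes the interpretation in advance.

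The programme being tested changes how often professionals see the family. The nurses who might raise a concern deliver the intervention, so they know the allocation. Researcher blinding, which the article states, protects the questioning and the video scoring. It does not reach a difference that arises before the mother is asked.

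There is a second filter. The counts exist only for mothers who complete the 12-month visit, and the Sample size section expects 30% dropout. A mother whose child has been removed may be harder to retain.

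These counts are the measure closest in name to maltreatment, and commissioners would take the label literally. A difference produced by detection or by loss could be reported as harm or as benefit, and a true effect could be hidden.

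**Working it through.** The article gives no event rate, detection rate or power for these counts, so it has no figure of its own to reproduce.

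**1. Contact.** Thirty infancy sessions over 52 weeks is 52/30 = 1.7 weeks per session, consistent with weekly or fortnightly meetings. No control figure is available, so the excess contact cannot be quantified.

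**2. Model.** Let d be the probability that true abuse leads to a recorded event. Let r be the probability that a mother with such an event reports it at 12 months. Then

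apparent RR = true RR × (d in gFNP / d in control) × (r in gFNP / r in control).

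Reading the counts as incidence requires the last two factors to multiply to 1. Nothing in the article secures that.

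**3. Size of the detection factor.** The Background says abuse of very young children may be up to 25% above official estimates. Official ascertainment is then at least 1/1.25 = 80%. Assume that this applies to these counts, that control detection is at that 80%, and that r is equal in both arms.

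| gFNP detection | Detection ratio | Apparent RR, no true effect | Apparent RR, true RR 0.80 | Apparent RR, true RR 0.52 |
|---|---|---|---|---|
| 80% | 1.00 | 1.00 | 0.80 | 0.52 |
| 100% | 1.25 | 1.25 | 1.00 | 0.65 |

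The value 0.52 is the 48% reduction that the Background cites for the home-based programme by age 15. It is used only as a reference size, since the horizon and the programme differ.

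**4. The opposing factor.** A reporting ratio of 1/1.25 = 0.80, meaning affected gFNP mothers supply the report 0.80 times as often as affected controls, would cancel a detection ratio of 1.25. With equal detection, the same ratio would give an apparent RR of 0.80 with no true effect. The article does not allow either ratio to be estimated.

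**5. Precision.** With 100 per arm and 30% loss, about 70 per arm remain. If the recorded control rate were 5% or 10% (assumed), that is 3.5 or 7 expected control events. Power for a 48% reduction would then be about 11% or 19%.

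**The case against.** The strongest reply is that the authors saw the detection problem and moved the primary inference to AAPI-2 and CARE. The three counts are introduced as an addition, and the main objective concerns parenting and risk factors, not abuse incidence. That stands: the counts are supplementary, and neither the primary outcomes nor the sample size is touched.

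A reader might infer more, namely that the comparison is biased against gFNP. The documents do not support a stated direction. Part of the gFNP contact replaces routine midwifery and infant checks. It takes place in groups in community settings. Controls also see midwives and health visitors and receive developmental reviews. Nurses may resolve a concern without referral, and loss of mothers whose child was removed could lower the gFNP counts. Extra detection is a plausible expectation for one factor, not a finding about the net result.

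A reader might also take the distortion to be larger, with a risk ratio of 1.5 or 2.0. That needs control detection near 50% and gFNP detection of 75% to 100%. The article gives no such figures, and its own under-ascertainment figure points to a ratio no higher than about 1.25.

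The Outcomes part of Data analysis promises every effort to obtain outcomes and would consider inverse probability weighting under larger or differential attrition. That may help with missing visits. It cannot correct unequal detection, nor loss that depends on the unobserved event itself. An analysis plan that is not shown could add caveats, but the label is already fixed in the article.

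Finally, HES attendance is not a neutral substitute. The programme aims to increase use of local services, and calling an injury non-accidental rests on professional suspicion. That stands, and it limits what HES can be asked to show.

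**Conclusion.** The concern holds as a point about labelling and interpretation. The three counts measure child-protection service activity as reported by mothers who complete the 12-month visit. They cannot carry a conclusion on the incidence of abuse, because detection and reporting may both differ by arm and the net direction is uncertain.

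The detection factor alone gives an apparent risk ratio of 1.0 to 1.25 with no true effect. This rests on three assumptions: that the Background's 25% figure applies to these counts, that control detection is 80%, and that reporting is equal in both arms. At the upper end a true 20% reduction would disappear. The small number of events expected makes a conclusion on incidence weaker still.

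**What to change.** 1. In Primary outcome measures, rename the three counts as child-protection service activity reported by the mother. Report them descriptively by arm, state that detection may differ between arms, and draw no conclusion on abuse incidence from them.

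2. Count A&E attendances for injury or ingestion directly from the HES extract already planned under Data management. Do this for all linked randomized infants, including those without a 12-month visit, instead of using HES only to confirm attendances.

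3. If nurse-initiated referrals are recorded, use them for description only. The record has no control counterpart, and some of those referrals would have happened anyway, so they must not be subtracted from the gFNP arm.

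The cost is wording and a broader use of data already to be obtained, with no extra participants or visits. The downside is that HES events will be few, so the comparison will be imprecise. HES is also less exposed to differences in service use, but not free of them.

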#### Secondary outcome measures

Secondary outcomes will assess socio-emotional aspects of parenting and family life and service use. Maternal depression will be assessed (baseline, 2, 6 and 12 months postpartum) using the Edinburgh Postnatal Depression Scale [44], a well-validated 12 item measure of postnatal depression with high reliability (0.88) and internal consistency (0.87), 86% sensitivity and 78% specificity. This questionnaire will be scored within 24 hours of its administration so that any woman with a total score above the recommended cut-off indicating a risk of depression, or who responds affirmatively to the question asking about self-harm, can be identified and a health care professional contacted to give appropriate support.

Maternal stress will be assessed (2 and 12 months postpartum) using the Abidin Parenting Stress Index, Short Form [45], a well-validated 36 item measure of perceived stress in the parenting role with sound test-retest reliability (r = .84) and internal consistency (a = .91). High scores on the PSI have been associated with abusive parenting [46,47] with some evidence that parenting stress is higher in women with five or more risk factors for child abuse [48]. In addition, parenting sense of competence will be assessed with the Parenting Sense of Competence (PSOC) scale [49] at two and twelve months. This 17 item measure has three factors; satisfaction, efficacy and interest established by factor analysis in a normative non-clinical sample, each with acceptable internal consistency (from 0.62 to 0.72) [50]. Maternal health-related quality of life (HRQoL) will be assessed using the EuroQol EQ-5D-5 L measure [51] at baseline, two, six and twelve months postpartum. This contains a visual analogue scale asking patients to rate their current HRQoL on a scale from 0 to 100, and a five dimension health status classification system, which can then be converted to a multi-attribute utility score by applying a UK tariff [52]. Brief questions designed for the study and based on those developed for use when delivering FNP will ask about maternal smoking, alcohol and drug use and relationship violence.

The extent of social support available to the mothers will be assessed (baseline and 12 months) using the Medical Outcomes Study (MOS) Social Support Survey [53]. The 20 item scale measures four dimensions of support, established using confirmatory factor analysis: emotional support, tangible support, positive interaction, and affection, each with internal consistency of 0.91 or higher, and also provided a total support score (Cronbach alpha 0.97); stability over time is also high for each scale (ranging from 0.72 to 0.78) [53]. Use of local resources and services will be assessed using questionnaires designed specifically for this study. Brief questions designed for the study will ask about infant feeding and the take-up of recommended immunizations in the infant’s first year.

#### Process measures

Data forms completed after each group session by the FNs delivering gFNP will provide information on intervention participants’ attendance at each session, the presence of partners and the extent of their understanding and involvement in the content. The ID number used by the FNs for program delivery data will be linked with the trial number.

Qualitative semi-structured interviews will be conducted with selected professionals in each locality to ascertain the extent to which the referral pathways could be strengthened, the likelihood that the service could be successfully embedded in the area and its likely sustainability. These interviews will take place after all recruitment has been completed in each local area with professionals likely, in the future, to be involved in making referrals to the program (in total, at least five community midwives and at least five other relevant health professionals such as general practitioners). At the completion of program delivery in each area, interviews will also be conducted with at least five commissioners of children’s services and with two professionals who are providers of care for ‘looked-after’ young people.

So that the research does not influence the experience of participants in the research, a number of interviews will be conducted after completion of program delivery in each group. At least one family nurse will be interviewed per center and each FNP supervisor will be interviewed about their thoughts on delivering the program and its likely sustainability. They will also be asked about the particular relevance of the gFNP program for women or their partners who have a ‘looked-after’ history or who are currently under the care of social services.

Participants’ views about the acceptability of the program will be assessed using semi-structured face-to-face interviews with a purposive sample (informed by program delivery data) of 20 women who were allocated to receive gFNP support and 5 of their partners.

In-depth semi-structured interviews will be conducted with up to 10 women allocated to receive gFNP (excluding those specified in the previous paragraph) who are or who have a history of being looked after and, if available, their partners, and a similar number of women allocated to standard care to explore their perceptions of the program, or any impacts, and other support needs.

